### 3.9. Training and Professional Regulation

All team members are certified to perform endovascular treatment using X-ray imaging units and have been trained prior to enrollment to ensure adherence to monitoring and safety governance, focusing on the study dose protocol and the “As Low As Reasonably Achievable” (ALARA) principles.

Verifications of internal dosimeters readings of all systems are performed annually by the Medical Physics Department following Spanish National Regulation [18] and the Radiology Quality Assurance Protocol of the Spanish Medical Physics Association [19]. If a calibration is needed, the technical service is contacted.

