## Abstract

In the past decades, we have witnessed tremendous developments in endovascular surgery. Nowadays, highly complex procedures are performed by minimally invasive means. A key point is equipment improvement. Modern C-arms provide advanced imaging capabilities, facilitating endovascular navigation with an adequate open surgical environment. Nevertheless, radiation exposure remains an issue of concern. This study aims to analyze radiation used during endovascular procedures according to complexity, comparing a mobile X-ray system with a hybrid room (fixed X-ray system). This is an observational and prospective study based on a cohort of non-randomized patients treated by endovascular procedures in a Vascular Surgery department using two imaging systems. The study is planned for a 3-year duration with a recruitment period of 30 months (beginning 20 July 2021) and a 1-month follow-up period for each patient. This is the first prospective study designed to describe the radiation dose according to the complexity of the procedure. Another strength of this study is that radiologic variables are obtained directly from the C-arm and no additional measurements are required for feasibility benefit. The results from this study will help us determine the level of radiation in different endovascular procedures, in view of their complexity.

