### 3.6. Outcome Measures

Peak skin dose (PSD) is the primary outcome of this study. PSD is defined as the maximum absorbed dose to skin from exposure to X-rays [20]. Secondary outcomes are described in Table 1 [2,3,4,5,6,7].

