### 3.7. Data Collection

The main source of information is the patient’s medical history and anamnesis. Radiological dose reports will be collected directly from the devices, including the main radiation dose metrics.

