### 3.8. Data Variables

#### 3.8.1. Imaging Systems

The X-ray device used on each procedure will be described as a dichotomous variable: Mobile C-arm (MCA) or hybrid room (HR). The MCA equipment is Zenition 70^®^ (Philips, The Netherlands) with a 30 × 30 cm flat-panel detector. The C-arm is color-coded and fully balanced with ability to angulate from +90 to −50° [21].

Philips Azurion 7^®^ is the X-ray equipment in a HR with a 20” flat detector and equipped with a workstation for image processing and fusion imaging (VesselNavigator, Phillips Healthcare, Best, The Netherlands). All compatible applications in the interventional lab via the central touch screen module and FlexVision Pro [22].

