## 4. Study Procedures

Identify patients with scheduled endovascular procedures.Once the patient is scheduled for endovascular surgery, we will explain the study and request their participation. If the patient agrees to participate, they will sign an informed consent document.The procedure will be scheduled either in the hybrid room or in the conventional room with a mobile C-arm, according to their availability.Collect information about medical history and anthropometric data during the interview and from the medical records in a database.The scheduled endovascular procedure will be carried out according to standard clinical practice.Obtain radiation dose parameters extracted directly from Philips Azurion^®^ and Philips Zenition 70^®^.If the endovascular procedure exceeds the radiation dose threshold (DAP ≥ 500 Gy·cm^2^, PSD ≥ 2000 mGy or AK ≥ 2000 mGy), the coordinating researcher will receive an alarm and will perform a patient clinical evaluation looking for any warning symptoms or signs.
In case of not finding signs of radiodermatitis, the patient will be informed of the warning signs, we will provide an information sheet, and preferential outpatient check-ups will be scheduled.In case of presenting clinical signs of radiodermatitis, the patient will be evaluated by a dermatologist.Based on standard clinical practice, patients will be assessed at one month.

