### 5.2. Statistical Analysis

We will perform a general descriptive analysis of the study variables. The results will be expressed as means and standard deviation, median, maximum, and minimum value, range and third quartile for the quantitative variables and for the categorical variables, the absolute and relative frequencies of each category. All study variables will be described, and descriptive statistics will be used according to the nature of the variable.

The principal analysis is the peak skin dose and other radiation dose variables described in Table 1. It will be analyzed by indirect radiological parameters, such as KAP or PSD. The secondary research will include:− The study population will be described according to the baseline characteristics and the type of procedure.− The procedure performed according to X-ray device used (mobile vs. fixed) and the level of complexity of the procedure will be described.− Partnership studies will be carried out.

Estimators will be accompanied by a 95% confidence interval. Statistical significance has been set at a probability level of <0.05.

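### Each system's dose is read only by its own internal dosimeter, and the article describes no use of the annual verification result on the study data, so a residual calibration difference would appear as a device effect

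*Protocol article*

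**What the plan says.** The primary objective (section 2.1) compares a mobile system with a hybrid room, and section 3.8.1 records the device as a two-level variable with one named model at each level. Section 3.6 states: "Peak skin dose (PSD) is the primary outcome of this study". Air kerma (AK) and kerma-area product (KAP) are among the further measures in Table 1.

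The dose data come from the machines. Section 3.7: "Radiological dose reports will be collected directly from the devices, including the main radiation dose metrics". The steps in section 4 have the same content for both systems, beginning "Obtain radiation dose parameters extracted directly from Philips Azurion". The Abstract presents this as a strength: "radiologic variables are obtained directly from the C-arm and no additional measurements are required for feasibility benefit".

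Section 3.9 deals with dosimeter accuracy: "Verifications of internal dosimeters readings of all systems are performed annually by the Medical Physics Department", under national regulation and a named quality assurance protocol. It then adds: "If a calibration is needed, the technical service is contacted". It gives no tolerance and does not say what happens to study readings when a verification finds a deviation. On the principal outcome, section 5.2 says: "It will be analyzed by indirect radiological parameters, such as KAP or PSD".

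**The concern.** The exposure being compared is also the measuring instrument. Every hybrid-room dose is read by one system and every mobile dose by the other, and no common or independent dosimeter is planned. If the two systems display the same true dose differently, the ratio of their readings is fully confounded with device. Stratifying by complexity, adjusting for body mass index or recruiting more patients cannot separate the two. The 95% confidence interval in section 5.2 covers sampling error only.

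The action described in section 3.9 is a maintenance rule. A dosimeter judged not to need calibration keeps its residual error in every record. If one system is recalibrated during the 30-month recruitment, the scale shifts part-way through that arm and not in the other. The mobile-versus-hybrid comparison is at stake, and so are the diagnostic reference levels (first secondary objective, section 2.2), which would inherit any absolute error.

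**Working it through.** **Figure to reproduce.** There is none. The article states no power, effect size, dose SD, tolerance or device split. Section 5.1 forecasts 150 to 200 procedures a year and section 3.2 gives 30 months of recruitment, so N = 150 × 2.5 = 375 to 200 × 2.5 = 500.

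**Assumptions (not in the article).** Log-normal dose with geometric SD 2.5, so the log SD is ln 2.5 = 0.916. Equal split, so n = 187.5 or 250 per device. No true device difference, a constant reading ratio b between the systems, and a two-sided test at 0.05.

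**Bias.** If the systems read true dose with factors k1 and k2, the estimated ratio of geometric means under no true difference centres on b = k1/k2, whatever the sample size.

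**Chance of p<0.05.** SE = 0.916 × √(2/n), z = ln b / SE, and P = Φ(z − 1.96) + Φ(−z − 1.96). SE is 0.0946 for n = 187.5 and 0.0820 for n = 250.

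| Scenario | b | ln b | z (N = 375; 500) | P (N = 375; 500) |
|---|---|---|---|---|
| No reading difference | 1.00 | 0 | 0; 0 | 5%; 5% |
| One device 10% high | 1.10 | 0.0953 | 1.01; 1.16 | 17%; 21% |
| Opposite errors of 5% | 1.05/0.95 = 1.11 | 0.1001 | 1.06; 1.22 | 18%; 23% |
| Opposite errors of 10% | 1.10/0.90 = 1.22 | 0.2007 | 2.12; 2.45 | 56%; 69% |

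Errors in the same direction cancel: if both systems read 10% high, b = 1.10/1.10 = 1.00. The opposite-error rows are therefore the worst case for their size. If the two errors are independent and uniform within ±10%, P averages about 14 to 17% and the median false ratio is about 1.06. Within ±5%, P averages about 7 to 8%.

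**Sensitivity to the assumptions.** Taking log SD from 0.6 to 1.2 and a split of 50:50 or 30:70, P runs from 11 to 43% at b = 1.10 and from 27 to 93% at b = 1.20.

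**Which outcomes are affected.** The mechanism applies directly to AK and KAP. It reaches peak skin dose only as far as that is derived from the device readings. Sections 4 and 5.2 suggest that it is, but the article does not say how either system obtains it. Fluoroscopy time, number of DSA series and contrast volume do not depend on dosimeter calibration.

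**The case against.** A reader might infer that doses will be compared uncorrected. The article does not say so. Sections 3.7 and 4 say where the data come from, not how they are processed afterwards, and a condensed article may leave correction factors to the full protocol, the analysis plan or the physics records. This stands: the absence of correction is an inference from the data path described.

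Section 3.9 is also itself a safeguard. The same department verifies all systems every year under a named protocol, with service contact if calibration is needed. What remains is error within tolerance and drift between checks. This stands too, and it limits the likely size.

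A reader might also take the 56 to 69% as the expected false-positive rate. It is the result for equal and opposite 10% errors, and nothing in the article suggests that pattern or any particular deviation. Nor can it be said that peak skin dose, AK and KAP are affected alike.

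Finally, annual verification does not prove that a usable ratio of reference to displayed reading was kept for each system and metric. That is fair, and the fix needs a fallback.

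None of this removes the confounding. The article takes up dosimeter accuracy, data extraction and analysis, and the only action on dosimeter error that it describes is a service call.

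**Conclusion.** The point holds as a structural weakness with an inexpensive remedy. Any residual reading ratio between the systems passes one for one into the mobile-versus-hybrid contrast for AK and KAP, and for peak skin dose as far as it is derived from them. An absolute error in either system's readings carries into the reference levels.

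The documents do not establish that a calibration difference exists, how large it could be, or that the readings will certainly go uncorrected. The rates shown rest entirely on the assumed dose spread, device split and error size. On those assumptions, a modest error in one system is enough to raise the false-positive rate to three or four times the nominal 5%. This is a worthwhile improvement to the plan, not a defect that by itself invalidates the study.

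**What to change.** In sections 3.9 and 5.2:

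- State the verification tolerance.
- Multiply AK, KAP and any peak skin dose derived from them by the device-specific factor (reference reading divided by displayed reading) from the verification covering the procedure date. Use a new factor after any recalibration.
- Use corrected doses for the device comparison and the reference levels, and show uncorrected doses as a sensitivity analysis.
- If a usable factor was not recorded, report the device ratio over the range that the tolerance allows. For a tolerance of ±t on each system, divide the observed ratio by values from (1−t)/(1+t) to (1+t)/(1−t).

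If correction is already specified elsewhere, a sentence in section 3.9 saying so settles the point.

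The cost is a short paragraph, retrieval of the verification records and one multiplication per record. The factors bring some uncertainty of their own, and drift between annual checks stays uncorrected. No new patient measurement is needed.

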## 4. Study Procedures

Identify patients with scheduled endovascular procedures.Once the patient is scheduled for endovascular surgery, we will explain the study and request their participation. If the patient agrees to participate, they will sign an informed consent document.The procedure will be scheduled either in the hybrid room or in the conventional room with a mobile C-arm, according to their availability.Collect information about medical history and anthropometric data during the interview and from the medical records in a database.The scheduled endovascular procedure will be carried out according to standard clinical practice.Obtain radiation dose parameters extracted directly from Philips Azurion^®^ and Philips Zenition 70^®^.If the endovascular procedure exceeds the radiation dose threshold (DAP ≥ 500 Gy·cm^2^, PSD ≥ 2000 mGy or AK ≥ 2000 mGy), the coordinating researcher will receive an alarm and will perform a patient clinical evaluation looking for any warning symptoms or signs.
In case of not finding signs of radiodermatitis, the patient will be informed of the warning signs, we will provide an information sheet, and preferential outpatient check-ups will be scheduled.In case of presenting clinical signs of radiodermatitis, the patient will be evaluated by a dermatologist.Based on standard clinical practice, patients will be assessed at one month.

## 5. Statistical Analysis

### 5.1. Sample Size Calculation

This research focuses on endovascular operations carried out in a high surgical volume. The number of procedures performed throughout the recruitment period will determine the sample size, which is anticipated to be between 150 and 200 endovascular procedures annually.

### 5.2. Statistical Analysis

We will perform a general descriptive analysis of the study variables. The results will be expressed as means and standard deviation, median, maximum, and minimum value, range and third quartile for the quantitative variables and for the categorical variables, the absolute and relative frequencies of each category. All study variables will be described, and descriptive statistics will be used according to the nature of the variable.

The principal analysis is the peak skin dose and other radiation dose variables described in Table 1. It will be analyzed by indirect radiological parameters, such as KAP or PSD. The secondary research will include:− The study population will be described according to the baseline characteristics and the type of procedure.− The procedure performed according to X-ray device used (mobile vs. fixed) and the level of complexity of the procedure will be described.− Partnership studies will be carried out.

Estimators will be accompanied by a 95% confidence interval. Statistical significance has been set at a probability level of <0.05.

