## Figures and Tables

**Table 1 mps-06-00049-t001:** Description of other radiation dose measures.

Parameters	Description
**Air kerma (AK)**	Represents the kinetic energy released per unit mass when an X-ray beam travels through air. The unit is milliGrays (mGy). It will be recorded by the system.
**Air-kerma area product (KAP or dose area product, DAP)**	The KAP is the product of two factors, namely the air kerma free in the air over the area of the X-ray beam in a plane perpendicular to the beam axis.
**Fluoroscopy time (FT)**	The time of exposure to X-ray, expressed in seconds. Fluoroscopy is a radiographic technique used for the visualization of anatomical structures in motion that allows guiding different diagnostic and therapeutic procedures in real-time. The unit is seconds. It will be recorded by the system.
**Contrast volume**	The total volume of contrast injected into the patient during the procedure. The unit is milliliter (mL).
**Body mass index (BMI)**	The measure of the weight compared to the height. The total amount of dose delivered will be correlated with patient size and weight.
**Number of DSA series**	The total number of digital subtraction series.
**Procedure time**	The total time interval from the start and end of the procedures, recorded in minutes (min).
**Type of anesthesia**	Described as general or loco-regional.

**Table 2 mps-06-00049-t002:** List of endovascular procedures.

Endovascular Procedures	Description
(1) Endovascular exclusion of abdominal aortic aneurysm	Placement of stent graft for internal lining of the aorta to exclude abdominal aneurysm.
(2) Endovascular exclusion of thoracic aorta	Placement of stent graft for internal lining of the thoracic aorta to exclude aneurysm, dissection, intramural hematoma, penetrating aortic ulcer or traumatic aortic injury.
(3) Endovascular exclusion of thoracoabdominal aortic aneurysm	Placement of stent graft for internal lining of the aorta to exclude thoraco-abdominal aneurysm.
(4) Endoleaks repair	Procedures that involve repairing blood flow between the graft and the aneurysm.
(5) Iliac percutaneous transluminal angioplasty or recanalization	Flow restoration procedure of the iliac sector through dilation with balloon catheter, with or without stent placement.
(6) Iliac stent	Stent placement in the iliac sector.
(7) Femoropopliteal percutaneous transluminal angioplasty or recanalization	Flow restoration procedure of femoropopliteal sector with or without stent placement.

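### Peak skin dose is the sole primary outcome in section 3.6, but section 5.2 makes other Table 1 dose variables part of the principal analysis, with one 0.05 level and no ordering

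*Protocol article*

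**What the plan says.** Section 3.6 (Outcome Measures) is plain: "Peak skin dose (PSD) is the primary outcome of this study". It continues: "Secondary outcomes are described in Table 1". Table 1 contains AK, KAP (also called DAP), fluoroscopy time, contrast volume, BMI, number of DSA series, procedure time and type of anesthesia.

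Section 5.2 (Statistical Analysis) sets out a different hierarchy: "The principal analysis is the peak skin dose and other radiation dose variables described in Table 1". The following sentence reads: "It will be analyzed by indirect radiological parameters, such as KAP or PSD". The secondary research listed after it covers description of the population, description of procedures by device and complexity level, and a third item that is not explained. The Table 1 dose measures are not in that list.

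The only error-rate statement is: "Statistical significance has been set at a probability level of <0.05". Estimators are to carry 95% confidence intervals. No test is named, and no order or allocation among the variables is given. Section 2.1 states the primary objective as a comparison of the mobile system with the hybrid room according to complexity.

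**The concern.** The two sections assign the same variables to different ranks. Under section 3.6, KAP is a secondary outcome. Under section 5.2 it belongs to the principal analysis, and it is then named as an alternative to PSD in an open-ended list of examples. Someone who has only section 5.2 cannot tell which metric carries the main device comparison.

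The metrics need not agree. By Table 1, KAP combines air kerma with the area of the X-ray beam, whereas section 3.6 defines PSD as a maximum skin dose. The two systems also have different detectors (section 3.8.1: 30 × 30 cm against 20 inches). The documents do not show that the metrics will diverge, but nothing guarantees that they will point the same way.

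The headline result is at stake. If the metric can be chosen after the data are seen, and each is judged at 0.05, the stated 5% no longer describes the risk that the reported principal finding arose by chance.

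**Working it through.** **Step 1. Set the two sections side by side.**

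| Variable | Section 3.6 | Section 5.2 |
|---|---|---|
| PSD | primary | principal |
| AK | secondary (Table 1) | principal (Table 1 dose variable) |
| KAP | secondary (Table 1) | principal, and named as an alternative to PSD |
| Fluoroscopy time, DSA series | secondary (Table 1) | principal if counted as dose variables |

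The conflict is certain for AK and KAP, which Table 1 describes as dose quantities: "Represents the kinetic energy released per unit mass when an X-ray beam travels through air" and "The KAP is the product of two factors, namely the air kerma free in the air over the area of the X-ray beam". Fluoroscopy time is a duration and DSA series a count, so including them is a matter of reading. Contrast volume, BMI, procedure time and anesthesia type are not radiation dose variables and are left out.

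**Step 2. Inputs.**
- Level per test: 0.05 (section 5.2; sidedness is not stated, and two-sided is assumed here).
- Number of principal metrics, k: 1 under section 3.6. Under section 5.2, 3 on the narrow reading (PSD, AK, KAP), 4 with fluoroscopy time, or 5 with DSA series too. These counts are an assumption about how the sentence is read.
- Correlation between metrics: not given in the documents, so a range of 0 to 0.9 is used.
- Decision rule: any one significant metric can be presented as the principal result. This is also an assumption.

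**Step 3. Reproduce the stated level.** The chance of at least one false positive among k independent tests is 1 − 0.95^k. For k = 1 this is 1 − 0.95 = 0.05, the plan's own figure and what section 3.6 implies.

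**Step 4. Apply it to section 5.2, independent metrics.**
- k = 3: 1 − 0.95³ = 0.143
- k = 4: 1 − 0.95⁴ = 0.185
- k = 5: 1 − 0.95⁵ = 0.226

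**Step 5. Allow for correlation.** Dose metrics from the same procedure can be expected to be positively correlated, so the figures in step 4 are upper ones. Simulating equally correlated normal test statistics, two-sided at 0.05, with 1,000,000 draws per setting, gives:

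| Assumed correlation | k = 3 | k = 4 | k = 5 |
|---|---|---|---|
| 0.5 | 12.5% | 15.6% | 18.3% |
| 0.7 | 10.9% | 13.0% | 14.9% |
| 0.9 | 8.4% | 9.4% | about 10% |

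Every setting exceeds 5%, but by an amount that depends heavily on assumptions the documents cannot settle.

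**The case against.** The strongest reply is that section 5.2 is mainly descriptive. It opens with descriptive statistics, names no test, and contains no rule that success on any one metric counts. The article condenses a fuller document, and handling of multiplicity is commonly left to that document or to an analysis plan. This stands as far as it goes: the absence of an adjustment is not a fault here, and the article does not say that its tests will be unadjusted. It does not remove the contradiction. A later plan can add detail, but the published text would still rank the same outcomes in two incompatible ways.

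Three stronger readings are tempting and should not be made.

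- A reader might multiply five metrics by three complexity levels and quote 1 − 0.95^15 = 54%. Nothing in the article plans a separate significance test in each level. Section 5.2 mentions device and complexity under secondary research, as things to be described.
- A reader might conclude that the study has no primary outcome at all. Section 3.6 still names PSD, and the authors can be held to it.
- A reader might object that BMI and anesthesia type appear among the outcomes. The BMI row already treats BMI as something to relate to dose ("The total amount of dose delivered will be correlated with patient size and weight"), as does the fourth secondary objective in section 2.2. No test of either as an outcome is planned, so relabelling them would change no result.

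**Conclusion.** The contradiction is real and lies in the current text: AK and KAP, at least, are secondary in section 3.6 and principal in section 5.2, and the sentence offering KAP or PSD leaves the principal metric open. Confidence in this is high.

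The size is conditional. If each metric were tested at 0.05 and any one could serve as the main result, the false-positive risk would be 14% on the narrow reading if the metrics were independent, and 23% on the wide reading. At assumed correlations of 0.9 to 0.5 the ranges are about 8% to 12% and about 10% to 18%. These figures show what the ambiguity would permit, not what the plan says it will do. The text should be corrected, because the point bears on the headline device comparison and the correction is simple.

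**What to change.** Rewrite section 5.2 to agree with section 3.6:

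- State that the sole principal analysis is the comparison of PSD between the mobile C-arm and the hybrid room, accounting for complexity level, as one test at 0.05. Report estimates by complexity level with 95% confidence intervals alongside it. Complexity has to be in this comparison: the primary objective in section 2.1 is framed by it, patients are not randomized, and rooms are assigned by availability (section 4).
- Delete the sentence that offers KAP or PSD as examples of the metric.
- List AK, KAP, fluoroscopy time and DSA series as secondary analyses, and state that none of them can replace PSD as the main result.

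With one principal test the false-positive risk returns to 5%. The change is to wording only and needs no further data or patients. The downside is fewer headline claims on the secondary metrics.

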## 2. Aims and Objectives

### 2.1. Primary Objective

This study aims to analyze radiation used during endovascular procedures according to complexity, comparing a mobile X-ray system (Philips Zenition 70 ^®^) with a hybrid room (Philips Azurion ^®^).

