(8) Femoropopliteal stent	Stent placement in the femoropopliteal sector.
(9) Infrapopliteal percutaneous transluminal angioplasty	Flow restoration procedure of the infrapopliteal sector through dilation with balloon catheter.

**Table 3 mps-06-00049-t003:** Complexity levels of endovascular procedures.

Low Complexity
A. Angioplasty of any territory
1. Arterial puncture without incidents 2. The guide passes easily without requiring specific material changes or multiple attempts 3. Absence of complication in the final angiogram 4. No arterial access complications
**Medium Complexity** (if any of the following are true)
A. Angioplasty of any territory
1. Difficult arterial puncture but achievable 2. Contralateral approach 3. Laborious recanalization of the stenosis/occlusion requiring one of the following conditions: guidewire/catheter changes collaboration of a second vascular surgeon 4. Presence (or not) of residual dissection on final angiogram 5. Presence (or not) of complications of arterial access
B. Angioplasty and stenting of any territory: whenever a stent implant is required, it will be of medium complexity (at least)—TASC A/B (aortoiliac), GLASS 1–2.
C. Recanalization of any territory—TASC A/B (aortoiliac)
D. Aortic endoprosthesis
1. An arterial approach without incidents (open or percutaneous) 2. Non-hostile anatomy (neck length > 15 mm and/or neck diameter < 32 mm, length of iliac arteries > 15 mm and/or diameter <20 mm) 3. Implantation of the device without incident 4. Easy catheterization of the contralateral limb 5. Absence of endoleaks in the final angiographic control (except type II)

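### The principal analysis in Section 5.2 omits the mobile versus hybrid-room comparison that is the primary objective, and complexity level alone does not make the rooms comparable in the Medium and High levels

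*Protocol article*

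**What the plan says.** Section 2.1 states the primary objective: "This study aims to analyze radiation used during endovascular procedures according to complexity, comparing a mobile X-ray system" with a hybrid room. Section 3.6 fixes the endpoint: "Peak skin dose (PSD) is the primary outcome of this study".

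Section 5.2 then says: "The principal analysis is the peak skin dose and other radiation dose variables described in Table 1". Neither device nor complexity appears in that definition. Both appear only in the list of secondary research: "The procedure performed according to X-ray device used (mobile vs. fixed) and the level of complexity of the procedure will be described". The remaining item in that list is "Partnership studies will be carried out", which is not defined. The same section sets a 5% significance level and asks for 95% confidence intervals.

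On allocation, Section 4 says: "The procedure will be scheduled either in the hybrid room or in the conventional room with a mobile C-arm, according to their availability". Section 3.1 calls the cohort non-randomized.

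On comparability, Section 3.8.3 presents the three complexity levels as the means to a reliable comparison across procedures, and the Conclusions repeat this for the two imaging systems. In Table 3:

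- Low contains angioplasty only.
- Medium contains angioplasty, stenting and recanalization (A to C) together with aortic endoprosthesis (D). Under B, "whenever a stent implant is required, it will be of medium complexity (at least"), in any territory.
- High contains limb work (A and B) together with aortic endoprosthesis (C), including fenestrated, branched and chimney techniques.

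Procedure type (Section 3.8.2, Table 2) and BMI (Table 1) are recorded. Section 5.2 brings neither into a device comparison.

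**The concern.** There are two linked problems.

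The first is a conflict inside the protocol. The question in Section 2.1 is a contrast between two devices by complexity. The principal analysis in Section 5.2 does not contain that contrast, and the only sentence with both factors is secondary and descriptive. Read literally, that sentence tabulates procedures by device and level, not dose. A significance threshold is set without saying which comparison it governs.

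The second is that the one comparability device on which the protocol relies, the complexity level, does not separate aortic from limb procedures in Medium and High. If those two kinds of procedure differ in dose and one room handles more of one kind, a contrast within a level mixes the effect of the device with the effect of the procedure. The study's main conclusion, which system gives more radiation at a given complexity, could then reflect scheduling.

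**Working it through.** **Step 1: the plan's own size.** Section 5.1 forecasts 150 to 200 procedures a year, and Section 3.2 gives 30 months (2.5 years) of recruitment.

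- 150 × 2.5 = 375 and 200 × 2.5 = 500 procedures.
- Assuming an even spread over 2 devices × 3 levels: 375/6 = 62.5 and 500/6 = 83.3 per device per level.

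This is a volume forecast. It has no effect size, SD or power, so there is no sample-size calculation to reproduce.

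**Step 2: objective against analysis.**

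| Element | Section 2.1 / 3.6 | Section 5.2, principal | Section 5.2, secondary |
|---|---|---|---|
| Dose outcome | Yes (peak skin dose) | Yes | Not named in the device item |
| Device contrast | Yes | No | Descriptive |
| Complexity | Yes | No | Descriptive |

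**Step 3: which levels mix aortic and limb work (Table 3).** Low: no aortic endoprosthesis entry. Medium: A to C with D. High: A and B with C. Aortic/limb mixing can therefore arise in Medium and High only.

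**Step 4: size of a false device effect.** Assumptions, none of them in the documents: no true device effect; aortic doses are R times limb doses; the log-SD within procedure type is s = 0.9; the aortic share of a level is p1 in one room and p2 in the other; n = 62 or 83 per device in the level.

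- False ratio of geometric means = R^(p1 − p2).
- Variance of log dose in a room = s² + (ln R)² p(1 − p).
- Standard error = √[(v1 + v2)/n]. The false-positive rate is from the normal approximation, two-sided 5%.

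Worked case: R = 2, shares 60% and 40%, n = 62. The false log ratio is 0.693 × 0.2 = 0.139, so the ratio is 1.15. Each variance is 0.81 + 0.480 × 0.24 = 0.925, so the SE is √(1.851/62) = 0.173. The standardized shift is 0.139/0.173 = 0.80, and the false-positive rate is 12.6%.

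| R | Aortic shares | False ratio | False-positive rate (n = 62 to 83) |
|---|---|---|---|
| any of 1.5, 2, 3 | 50% / 50% | 1.00 | 5% |
| 1.5 | 60% / 40% | 1.08 | 7.8 to 8.8% |
| 2 | 55% / 45% | 1.07 | 6.9 to 7.5% |
| 2 | 60% / 40% | 1.15 | 12.6 to 15.3% |
| 2 | 70% / 30% | 1.32 | 36.6 to 46.5% |
| 3 | 60% / 40% | 1.25 | 21.5 to 27.1% |
| 3 | 70% / 30% | 1.55 | 66.0 to 78.4% |

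**Step 5: set against sampling error in the same level.** The half-width of the 95% interval, as a factor, is exp[1.96 × SD × √(4/N)], where N is the number of procedures in one level, taken as a third of the cohort (125 to 167), with an assumed log-SD of 0.8 to 1.0.

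- N = 166.7, SD 0.8: exp(1.96 × 0.8 × 0.155) = 1.27.
- N = 125, SD 1.0: exp(1.96 × 1.0 × 0.179) = 1.42.

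False ratios of 1.07 to 1.25 lie inside this sampling noise, 1.32 is comparable with it, and 1.55 exceeds it.

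**Step 6: after adjustment.** In this illustration dose depends only on procedure type, so stratifying or adjusting for aortic versus limb within the level returns the false ratio to 1.00 and the false-positive rate to 5%.

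**The case against.** **No analysis plan is shown.** A condensed article may leave covariates, transformation and model form to one, and the undefined association item in Section 5.2 might cover some of this. That stands. A reader might infer that the comparison will be made without adjustment. The documents support only that no adjustment is stated. Deferral does not, however, explain a stated ranking of analyses that conflicts with the stated objective.

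**Imbalance between rooms is not documented.** Sections 1 and 4 tie room choice to equipment availability and scheduling, which could leave case mix balanced. That also stands. Section 3.8.1 mentions fusion imaging only for the hybrid room, so unequal case mix is plausible, but nothing says that aortic cases are sent there. The tempting claim that the plan will report a false device effect is not supported; it can, if shares differ.

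**Not every level is affected.** A reader might take all three levels to mix aortic and limb work. Table 3 contradicts that for Low.

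**Small imbalances do not dominate.** Set against a whole-cohort half-width (1.15 to 1.22 under the same SDs and N = 375 to 500), the false ratios look larger than they should. The bias arises within a level, and the matching half-width is 1.27 to 1.42.

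**Procedure type is not ignored.** Section 2.2 plans reference levels by procedure and complexity, and Table 3 lists aortic endoprosthesis separately, so the split is available. This shows that the repair is feasible, but the device comparison does not use it.

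**Complexity includes events during the procedure**, such as wire changes and access complications, which the imaging system might influence. This is a fair caution about conditioning on complexity, but the primary objective already does so.

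**Conclusion.** The point holds in two parts. The conflict between Section 2.1 and Section 5.2 is in the text and needs no assumption: the principal analysis does not contain the contrast that the study is meant to estimate.

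The confounding is a risk confined, as aortic/limb mixing, to the Medium and High levels. It needs two conditions that the documents do not quantify: a dose difference between aortic and limb work, and a different aortic share in the two rooms. With assumed dose ratios of 2 to 3 and share differences of 20 to 40 points, the false device ratio runs from about 1.15 to 1.55. Only the upper end exceeds per-level sampling error, although false-positive rates already exceed 5% at the lower end. With balanced shares there is no bias from this source. The matter deserves correction because the remedy is almost free and is credible only if fixed before the data are analyzed.

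**What to change.** In Section 5.2, replace the definition of the principal analysis with the device contrast (mobile versus hybrid room) in log peak skin dose by complexity level. Adjust for or stratify by Table 2 procedure type, at least aortic (items 1 to 4) versus limb (items 5 to 9) within Medium and High, and adjust for BMI. Report adjusted ratios of geometric means with 95% confidence intervals for each level. Keep the tabulation of procedures by device and level as a supporting display, since it will show whether case mix differs between rooms.

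The cost is a change of wording and slightly more analysis; procedure type and BMI are already recorded. Sparse procedure types may need to be grouped, and the grouping should be set before dose is examined by device. Further choices, such as restricting to strata performed on both devices, allowing for repeat procedures in one patient, or the exact interaction model, are optional and can sit in the analysis plan.
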